### Eligibility criteria and Multi-stage recruitment process

For this study, we use a database with the medical records of FMS patients referred from local general practices to the Rheumatology Service at Parc Sanitari Sant Joan de Déu to confirm diagnosis. The sample pool consists of all FMS patients included in this database between January 2010 and September 2015 (N_sample pool_ = 531). Thus, all patients in the database were diagnosed with FMS (according to the American College of Rheumatology, ACR 1990 criteria) by rheumatologists from Parc Sanitari Sant Joan de Déu.

Patients meeting the following criteria will be eligible: 1. Patients of both genders between 18–65 years-old. 2. Able to understand the Spanish language. 3. Provide informed consent to participate. The following *general exclusion criteria* will be applied: 1. Participation in other RCTs. 2. Presence of cognitive impairment according to the Mini Mental State Examination (MMSE < 27). 3. Receiving psychological treatment during the previous or current year. 4. Reporting previous experience in meditation or other mind-body therapies. 5. Comorbidity with severe mental or medical disorders which interfere with treatment (severe medical illness, psychotic symptoms, substance abuse). 5. Unable to attend group sessions. 6. Pregnancy. 7. Involved in ongoing litigation relating to FMS.

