Usual contraindications for scanning at 3Tesla and for measuring cytokine levels have been taken into account to establish the following additional inclusion/exclusion criteria for the biomarkers sub-study:*Inclusion criteria*: 1. Female gender. 2. Right-handed.*Exclusion criteria*: 1. Infection/cold symptoms on the day of blood extraction. 2. Needle phobia. 3. BMI > 36 kg/m^2^ or weight > 110Kg. 4. Neoplastic illnesses, infection, cardiopulmonary, vascular, or other internal conditions (collected from the medical history). 5. Use of oral or local corticosteroids or anticytokine therapy. 6. Consuming more than 7 caffeine units per day (1 caffeine drink will be permitted on the day of the study. 8. Smoking more than 5 cigarettes per day (no smoking will be permitted on the scanning visit days prior to scanning or whilst in the centre). 9. Cannot be evaluated by means of magnetic resonance imaging (MRI) (due to claustrophobia, metal implants, pace-makers, etc.). 10. Acute pain not -related to FMS on the day of the study (e.g. headache, lumbar pain). 11. Being pregnant or breastfeeding. It is important to point out that patients presenting neuroradiological alterations during MRI at baseline will be excluded from the sub-study. Patients will be allowed to continue with their stable medical treatment although, to reduce the effects of medications on biomarkers, they will be required to refrain from taking occasional (rescue) analgesic drugs (e.g., non-steroidal anti-inflammatory drugs, paracetamol) 72 h prior to the MRI and blood extraction. Changes in pharmacological/non-pharmacological treatment will be monitored throughout the study and may be a cause of drop-out from the final analyses.

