### Study measures

Study participants will complete the following instruments as part of a paper-and-pencil battery of measures (see Table 3):*Sociodemographic-clinical questionnaire*. The following information will be collected: gender, age, ethnic group, marital status, living arrangements, educational level, employment status, and annual income. Relevant clinical variables, such as family and personal medical history, years of FMS diagnosis and comorbid conditions will also be assessed.

**Table 3 Tab3:** Study periods at which measures and data are collected

Study measures	Baseline	During treatment	2 months	12-months
Demographic information (gender, age, etc.)	X			
History of FMS (years of illness)	X			
Contact details	X			
SCID-I (depression module)	X			
*Screening measures*				
MMSE (cognitive impairment)	X			
*Primary outcome measure*				
FIQR (functional impairment)	X		X	X
*Secondary outcome measures*				
FSDC (fibromyalginess)	X		X	X
HADS (anxiety and depression)	X		X	X
PSS-10 (perceived stress)	X		X	X
MISCI (subjective cognitive impairment)	X		X	X
EQ-5D-5L (quality of life)	X			X
CSRI (health economic evaluation)	X			X
FFMQ^a^ (mindfulness facets)	X		X	X
PCS^a^ (pain catastrophizing)	X		X	X
PIPS^a^ (psychological inflexibility)	X		X	X
SCS-12^a^ (self-compassion)	X		X	X
*Other measures*				
Structural + Functional Neuroimaging data	X		X	
Inflammatory data	X		X	
CEQ (Expectation/Satisfaction with treatment)	X (EXP)		X (SAT)	
PGIC & PSIC (Impression of change)			X	X
Treatment attendance form: Attendance at each scheduled MBSR/FibroQoL session		X		
Log of MBSR and FibroQoL practices		X		
Treatment fidelity (review of video-taped MBSR sessions) & monitoring of adverse events		X	X	X

*CEQ* Credibility/Expectancy Questionnaire, *CSRI* Client Service Receipt Inventory, *EQ-5D-5L* EuroQoL questionnaire, *FFMQ* Five Facet Mindfulness Questionnaire, *FIQR* Revised Fibromyalgia Impact Questionnaire, *FSDC* Fibromyalgia Survey Diagnostic Criteria, *HADS* Hospital Anxiety and Depression Scale, *MISCI* Multidimensional Inventory of Subjective Cognitive Impairment, *MMSE* Mini-Mental State Examination, *PCS* Pain Catastrophizing Scale, *PGIC & PSIC* Patient Global and Specific Impression of Change, respectively, *PIPS* Psychological Inflexibility in Pain Scale, *PSS-10* Perceived Stress Scale, *SCID-I* Structured Clinical Interview for DSM Axis I Disorders, *SCS-12* Self-Compassion Scale

^a^Secondary outcome measures that also considered process variables

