#### Secondary outcome measures and process measures

The *Fibromyalgia Survey Diagnostic Criteria* (FSDC) [59, 60] is a 6-item self-report questionnaire that registers the key symptoms of FMS according to the latest revision of the ACR. It includes assessment through the Widespread Pain Index (WPI) identifying 19 body areas (jaws, shoulders, upper arms, lower arms, hips, upper legs, lower legs, neck, chest, upper back, lower back and abdomen) where pain or tenderness was felt during the previous 7 days (total score 0–19). The Symptom Severity Scale (SS; range from 0–12) includes three major symptoms (fatigue, trouble thinking/remembering and waking up tired or unrefreshed), which is scored from 0 to 3, as well as three additional symptoms (pain or cramps in lower abdomen, depression, headache), which can be coded as present (1) or absent (0). The fibromyalgianess scale is defined as the sum of the WPI items (0–19) and the 6-item SS scale (0–12), so total scores can range from 0 to 31.The *Client Service Receipt Inventory* (CSRI) [61, 62] used for the present project will be designed to collect retrospective data on medication and service receipt: 1. Medication. A profile of the patient’s use of all prescribed medications (analgesics, non-steroidal anti-inflammatories, short- and long-acting opioids, etc.) will be requested, including the name of the drug, the prescriber, the dosage level, the total number of days taking the drug, the total dosage consumed, the reasons for changing the drug, and adherence. 2. Service receipt. We will collect information about emergency services, general medical in-patient hospital admissions and out-patient health care services. Patients will also be asked about type and number of diagnostic tests administered. As shown in Table 3, the CSRI will be administered at baseline and at a 12-month follow-up*; on both occasions, the previous 12 months will be reviewed*.The *EuroQoL-5D questionnaire* (EQ-5D-5L) [63] is a widely used health-related quality of life instrument with a non-disease-specific classification system composed of 2 parts: Part 1 is a self-reported description of health problems classified into five dimensions. Patients mark one of five degrees of severity in each dimension. The time frame is the day of responding. Part 2 records the current subject’s health on a Visual Analogue Scale (VAS); a vertical 10 cm line on which the best and worst imaginable health states score 100 and 0, respectively.The *Hospital Anxiety and Depression Scale* (HADS) [64, 65] was originally developed to quantify the severity of anxiety and depressive symptoms in non-psychiatric hospital patients The HADS includes a total of 14 items that assess anxiety (HADS-A) and depressive (HADS-D) symptoms, with 7 items in each subscale. Each item is answered on a four-point (0-to-3) scale so that possible scores range from 0 to 21 for both anxiety and depressive symptoms, with higher scores indicating greater severity.The *Perceived Stress Scale* (PSS-10) [66] is a 10-item, self-administered instrument that measures the degree to which situations in one’s life are considered stressful. Scores range from 0 to 72. The Spanish version of the PSS-10 has adequate reliability and validity [67].The *Multidimensional Inventory of Subjective Cognitive Impairment* (MISCI) [68] is a 10-item measure of perception of cognitive dysfunction in FMS, developed through classical test theory and item response theory from cognitive functioning item banks that were developed as part of the Patient Reported Outcomes Measurement Information System (PROMIS). The MISCI showed excellent internal reliability, low ceiling/floor effects, and good convergent validity with a similar measure.The *Pain Catastrophising Scale* (PCS) [69, 70] is a 13-item questionnaire derived partially from the Coping Strategies Questionnaire and other descriptions of catastrophising. It has three dimensions: Rumination (tendency to focus excessively on pain sensations), Magnification (tendency to magnify the threat value of pain sensations) and Helplessness (tendency to perceive oneself as unable to control the intensity of pain). The PCS total score and subscale scores are computed as the algebraic sum of ratings made for each item. PCS items are rated in relation to frequency of occurrence on 5-point scales (0 = never ~ 4 = almost always).The *Five Facet Mindfulness Questionnaire* (FFMQ) [71, 72] consists of 39 items that assess five facets of mindfulness. Items are rated on a Likert scale ranging from 1 (never or very rarely true) to 5 (very often or always true). The factors include: *Observing*, including noticing or attending to internal and external experiences such as sensations, thoughts, or emotions. *Describing* refers to labelling internal experiences with words. *Acting with awareness* involves focusing on one’s activities in the here and now as opposed to behaving mechanically. *Non-judging of inner experience* refers to taking a non-evaluative stance toward thoughts and feelings. Finally, *non-reactivity to inner experience* is allowing thoughts and feelings to come and go, without getting caught up in or carried away by them. In a recent online survey answered by 4,986 FMS patients from all 50 US states and 30 countries, the FFMQ subscales was shown to discriminate well among FMS patients self-identified as meditators or non-meditators. Overall, FMS patients with higher mindfulness scores had lower levels of FMS symptom severity as measured with the FIQR [73].The *Self-Compassion Scale-short form* (SCS-12) [74, 75] is a shorter version (12 items) of the SCS (26 items). The SCS was designed to assess overall self-compassion (total score) and components of self-compassion across three dimensions: common humanity, mindfulness and self-kindness. The SCS–SF shows good internal consistency (Cronbach’s α ≥0.86) and very high convergence with the long form of the scale (r ≥0.97).The *Psychological inflexibility in pain scale* (PIPS) [76, 77] is a 12-item scale designed to measure psychological inflexibility in pain patients. The instrument includes two factors: *avoidance* and *cognitive fusion* related to pain. The items consist of different statements that are considered to be related to chronic pain, psychological inflexibility, suffering and disability (coherent with the ACT theory). All the items are rated on a 7-point Likert-type scale that ranges from “1 = never true” to “7 = always true”, with higher scores indicating more psychological inflexibility.

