
#### Other measures

The *Patient Global Impression of Change (PGIC) and Pain Specific Impression of Change* (PSIC) [78] are measures that have been frequently used as indicators of meaningful overall change [on a 7-point Likert scale, from 1 = “Much better” to 7 = “Much worse”] in treatments for chronic pain, whereas the PSIC asks about the impression of change in more specific domains: physical and social functioning, work-related activities, mood, and pain.*Adapted version of the Credibility/Expectancy questionnaire* (CEQ) [79]. The CEQ is a 6-item questionnaire for measuring treatment expectancy and credibility for use in clinical outcome studies. The questionnaire shows overall high internal consistency (α = 0.84–0.85). We will use an adapted version that evaluates Expectancy (at the end of the first treatment session) and Opinion (at the end of the last treatment session) about MBSR and FibroQoL.*Log of out-session for MBSR and psychotherapeutic practices*. An *ad hoc* instrument for the weekly recording of formal and informal mindfulness or FibroQoL home practice. A recent systematic review of systematic reviews and a meta-analysis of standardised mindfulness interventions (MBSR and MBCT) indicated that an increase in total minutes of mindfulness practice and class attendance are associated with a reduction of stress and mood complaints [80].*Adverse events of the interventions. Ad hoc* measure to check for adverse events (e.g., anxiety, dizziness, sleep problems, etc.) across the interventions and follow-up.

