One of the main risks in this study may be dropouts. A sensitivity analysis using a per protocol strategy will be performed to determine the impact of the adherence to the protocol in both the MBSR and FibroQoL groups. This RCT is intended to be as naturalistic as possible, so prescribed drugs are permitted throughout the study. The effects of these drugs on clinical and biological outcomes may constitute another study limitation. However, no baseline differences among study arms regarding medical drugs are expected (due to randomisation) and sub-analyses evaluating the potential effects of the main pharmacological treatments (e.g., antidepressants) on the outcomes will be performed. Moreover, received pharmacological treatment may not be stable over time (e.g., initiating antidepressant treatment due to a depressive episode, changing principle/dose of other drugs due to variations in clinical symptoms, or starting individual therapy with a psychologist) so it is probable that some patients will be excluded from the study due to drastic changes in their treatment. Patients will be asked at post- and follow-up assessments for details about changes in medical treatment received and the clinicians will check the pharmacological treatment history in the patients’ clinical chart.

To our knowledge, this study represents the first attempt to detect structural and functional brain changes and inflammatory marker variations after MBSR in patients with FMS. Indeed, few studies have focused on exploration of the neural and inflammatory underpinnings of psychological treatments in chronic pain patients. We hope that our work will offer new advances in understanding the psychophysiological processes altered by mindfulness and their relationship with clinical outcomes. Understanding of how mindfulness changes these variables will in turn increase our understanding of the role of the brain and the immune system in FMS. Furthermore, determining FMS profiles according to psychological and brain/immune variables may also allow prediction of treatment response in patients with this diagnosis. Given that patients with FMS usually present comorbidities with psychiatric disorders (such as depression or anxiety) and other central sensitivity syndromes (such as chronic fatigue syndrome), the results from this study may have translational value.

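### The home-practice log stops with treatment, and no described 12-month measure specifically records continued or newly started mind-body practice in any arm

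*Protocol article*

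**What the plan says.** **At entry.** The general exclusion criteria include "Reporting previous experience in meditation or other mind-body therapies" (Eligibility criteria and Multi-stage recruitment process). The note to Table 2 adds that one FibroQoL session was removed because it touched on meditation, so that the comparator has no mindfulness content.

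**During treatment.** Table 3 has a row "Log of MBSR and FibroQoL practices" with one mark, in the during-treatment column, and none at 2 or 12 months. Other measures describes it as an ad hoc "instrument for the weekly recording of formal and informal mindfulness or FibroQoL home practice". No corresponding record is described for TAU.

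**After treatment.** Two places say how treatment changes are followed:
- Eligibility criteria, at the end of the biomarker sub-study paragraph: "Changes in pharmacological/non-pharmacological treatment will be monitored throughout the study and may be a cause of drop-out from the final analyses".
- Discussion: "Patients will be asked at post- and follow-up assessments for details about changes in medical treatment received", with a check of the pharmacological history in the chart. The sentence before it gives "starting individual therapy with a psychologist" as one example of a change, and expects that some patients will be excluded for drastic changes.

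**Other 12-month instruments.** The CSRI covers medication, diagnostic tests and "emergency services, general medical in-patient hospital admissions and out-patient health care services". The FFMQ is scheduled at baseline, 2 months and 12 months, with no restriction by arm.

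**Analysis.** Analysis of clinical efficacy specifies intention-to-treat with all randomised participants and multiple imputation.

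**The concern.** The design protects the mindfulness contrast up to the end of the programme, through the entry exclusion and the edited comparator, and then does not measure it directly. The article itself treats practice as important. Other measures cites evidence linking more practice minutes and attendance with less stress and fewer mood complaints, and the last MBSR session in Table 1 is about carrying practice on indefinitely.

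Effectiveness and cost-utility over 12 months are main objectives. If the 12-month FIQR difference is small, the team will want to know whether MBSR has no lasting effect, whether MBSR patients stopped practising, or whether control patients took up something similar. The described data do not address the last two directly. The mediation analysis has the same limit: its process variables are changes up to post-treatment, so practice between then and the 12-month outcome is not in the model.

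The second issue is scope. The two statements on treatment changes differ in what is tracked and perhaps in whom, yet both allow patients to be removed after randomisation.

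**Working it through.** **1. Length of the unrecorded period.** The programme has eight weekly sessions (Interventions), and the last assessment is 56 weeks after randomisation (Procedure). If sessions start close to randomisation, 56 − 8 = 48 weeks have no practice record in any arm.

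**2. What each described source could show at 12 months.**

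| Source | Continued MBSR or FibroQoL practice | New self-directed mind-body practice | New formal non-drug care |
|---|---|---|---|
| Practice log | No, ends with treatment | No | No |
| Question in Discussion | Not named | Not named | Psychologist named as an example |
| Monitoring sentence in Eligibility | Not named | Possibly, if seen as treatment | Yes, if it applies to all participants |
| CSRI | Not listed | Not listed | Out-patient services |
| FFMQ | Indirectly | Indirectly | No |

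The first two columns contain no direct measure. The FFMQ measures mindfulness facets, not type or amount of practice. It is also a secondary outcome and a process variable, so reading it as exposure mixes exposure with effect.

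**3. Consistency of the rules.** One statement covers pharmacological and non-pharmacological changes but stands in the sub-study paragraph. The other names medical treatment and drug history and stands in a general paragraph. Each mentions loss of patients for treatment changes. The efficacy section includes everyone randomised. If such patients are removed from the efficacy analysis, that rule is not met.

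**4. The plan's power figures.** Inputs from Participants: d = 0.53, alpha 0.05, 60 per group, and 60 × 0.8 = 48 after 20% attrition. Normal approximation: power = Φ(d√(n/2) − z).
- One-sided, z = 1.645, n = 60: 0.53 × √30 = 2.903; Φ(1.258) = 0.896. Stated: 0.89.
- One-sided, n = 48: 0.53 × √24 = 2.596; Φ(0.951) = 0.829. Stated: 0.82.
- Two-sided, z = 1.96: 0.827 and 0.738, which do not match.
- A three-arm ANOVA with f = d/2 gives 0.894 and 0.811, also close to the stated values.

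Sidedness is not stated, so both versions are carried forward.

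**5. Illustration of dilution.** If a share c of TAU takes up an equivalent practice and gains the full effect, the difference is d − cd = 0.53(1 − c). If instead a share c of MBSR lapses and loses the whole effect, the difference is again 0.53(1 − c). The between-arm FIQR difference alone cannot separate the two.

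| c (assumed) | d | Power, n = 48, one-sided | Power, n = 48, two-sided |
|---|---|---|---|
| 0 | 0.53 | 0.83 | 0.74 |
| 10% | 0.48 | 0.76 | 0.65 |
| 20% | 0.42 | 0.67 | 0.55 |
| 30% | 0.37 | 0.57 | 0.44 |

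The shares are assumptions. The documents give no uptake or lapse rate, so there is no corrected figure.

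**The case against.** A reader might infer that the trial follows only medical treatment, so that control uptake and MBSR lapse are wholly unseen and the 12-month result cannot be interpreted. The article does not support that.

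- Non-pharmacological changes are to be monitored throughout, and although the sentence closes the sub-study paragraph, it speaks of the study as a whole. Starting therapy with a psychologist is named in the Discussion. The narrower Discussion sentence does not deny the wider one.
- The FFMQ at 12 months in all arms should look different if controls took up mindfulness than if MBSR patients lapsed. The article also reports that its subscales separate self-identified meditators from non-meditators. The scenarios therefore need not give identical data.
- Intention-to-treat in a deliberately naturalistic trial estimates the effect of offering MBSR. Lapse and outside uptake are part of that effect, not errors in it.
- The dilution formula assumes that self-directed practice, or complete lapse, moves the whole programme effect. It is an upper bound for a given c, and the added items would describe dilution, not remove it.
- The article only summarises the CSRI, so one cannot say that it misses a yoga class or an app. Leaving out private spending follows from the cost definition in Cost-utility analysis.
- The article gives no reason for the entry exclusion. That it protects the contrast is an inference, supported by the Table 2 note.

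All of this stands. It does not touch the schedule itself: the log is marked only during treatment, and no described 12-month measure asks about practice.

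**Conclusion.** The point holds in a limited form. The practice log ends with treatment, about 48 weeks before the last assessment. No described 12-month measure specifically records continued practice in MBSR or FibroQoL, or newly started meditation or mind-body practice in any arm; the FFMQ signal is indirect. The two statements on treatment changes differ in scope, and the removals they allow sit badly with the intention-to-treat rule.

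The 12-month intention-to-treat contrast remains valid provided everyone randomised is kept. What is weakened is the explanation of a small or null difference, and with it the reading of the mediation results. The size is unknown: d of 0.48 to 0.37 for assumed shares of 10% to 30% is an illustration, not an estimate. The stronger readings, that uptake and lapse are invisible or that the 12-month comparison is uninterpretable, go beyond the documents. This is a cheap improvement to data that are hard to recover later, not a flaw in the primary comparison.

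**What to change.** 1. Reconcile the monitoring sentence in Eligibility criteria with the one in the Discussion, and state that pharmacological and non-pharmacological changes are recorded in the same way for all participants, not only the sub-study.
2. At the 2-month and 12-month assessments, add identical short self-report items in all three arms on meditation, yoga, other mind-body practice, self-hypnosis and psychological therapy since the previous assessment: type, number of weeks and minutes per week. Include continued MBSR or FibroQoL home practice. Put the items in the existing paper battery, so that the blinded interviewers need not ask about practice.
3. State that patients who report such practice or a treatment change stay in the intention-to-treat analysis, and align the two passages on exclusion with that rule.
4. Report continued practice and new uptake by arm beside the 12-month contrasts, as description and not as an adjustment.

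The cost is a few items at two existing visits, slightly more patient burden, and recall error over the long interval to the 12-month assessment.
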